### Trial feasibility assessment and design

Our trial progression criteria are: (1) the number of people who engage with either MINAP or PICANet data (via QualDash or some other means) is the same or higher than the number of people who engaged with either MINAP or PICANet data prior to QualDash’s introduction; (2) data completeness in the national audit improves or remains the same; (3) 50% or more of participants in the questionnaire survey perceive QualDash to be useful and express the intention to continue using it after the study period. Criteria (1) and (2) are concerned with ensuring the intervention does not have unintended negative consequences which would affect success of the intervention. Criterion (2) is also concerned with feasibility of outcome assessment. Criterion (3) is concerned with acceptability and uptake of the intervention, and therefore has implications for recruitment to a trial, as well as being concerned with participants’ perceptions of the impact of QualDash on care. While not formally assessed as part of the progression criteria, the impact of QualDash on care as identified in the CITS will be considered in determining whether a future trial is justified. A traffic light system will be used to determine if a trial is feasible (green), feasible with modifications to QualDash (amber), or not feasible (red).^58 59^

If the results show a trial of QualDash is feasible, we will design a stepped wedge cluster randomised trial. Data from the CITS will be used to inform the selection of NCAs to be included in the trial (MINAP and/or PICANet) and will provide information about variability of outcomes and about how long a trial intervention period would need to be. Findings from the multi-site case study will be used to inform the selection of categories of user to be included in the trial and, associated with this, the level of randomisation (Trust, hospital or ward). Using the understanding of the relationship between contexts, mechanisms and outcomes provided by the study, we will identify QualDash components associated with mechanisms that produce the desired outcomes in order for them to be preserved in the trial, while other components can be adapted to suit the local context.

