**Ethics and dissemination:**

The study has been approved by the University of Leeds School of Healthcare Research Ethics Committee. Study results will provide an initial understanding of how, in what contexts, and why quality dashboards lead to improvements in care quality. These will be disseminated to academic audiences, study participants, hospital IT departments and national audits. If the results show a trial is feasible, we will disseminate the QualDash software through a stepped wedge cluster randomised trial.

Strengths and limitations of this studyThis study will assess the feasibility of a trial of QualDash, a quality dashboard; if a trial is feasible, the findings will be used to inform the design of the definitive trial, determining the components of QualDash to be preserved, appropriate outcome measures and the contexts in which the trial should be undertaken.Through a controlled interrupted time series (CITS) study and qualitative multi-site case study, the study will also provide an initial understanding of whether the use of a quality dashboard leads to quality improvement, how, in what contexts, and why.The study will contribute to understanding of how realist methods can contribute to feasibility studies and the design of trials.Issues of data quality may be a limitation of the CITS study; data completeness, and whether this changes over the course of the study, will be assessed.

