Given the study intention to determine the feasibility of and inform the design of a trial, a range of measures will be considered. Initially, we selected two process measures, one for MINAP and another for PICANet. For MINAP, we selected the composite process measure cumulative missed opportunities for care (CMOC). This has nine components (pre-hospital ECG, acute use of aspirin, timely perfusion, referral for cardiac rehabilitation and prescription at hospital discharge of what are considered to be the gold standard drugs—aspirin, thienopyridine inhibitor, angiotensin converting enzyme inhibitor, β-Hydroxy β-methylglutaryl-CoA (HMG-CoA) reductase inhibitor and beta blockers) and is inversely associated with mortality.^54^ As some of these components, such as pre-hospital ECG, are outside the direct control of the Trust, we will also explore the impact of QualDash on the individual measures that make up CMOC. On the basis of the measures that cardiology clinicians described in the interviews as being important for measuring care quality, we will also look at the percentage of patients who receive an angiogram within 72 hours from first admission to hospital, which is part of the Best Practice Tariff financial incentive scheme, and, for those hospitals that provide percutaneous coronary intervention (PCI), the proportion of patients who have a door-to-balloon time (the time from arrival at the hospital to PCI) of less than 60 min. Our CMO configurations (online supplementary file 2) suggest improvement will be seen in measures if: clinical teams perceive them as being important indicators of care and/or they relate to financial incentives; performance is not in line with expectations; they perceive the measure as being within their control; and the team is resourced to introduce QI initiatives in relation to these measures.

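### Progression criterion 2 tests only whether data completeness falls, so it cannot show that outcomes can be assessed, which is its second stated purpose

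*Protocol article*

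**What the plan says.** The section on trial feasibility assessment and design in the protocol article lists three progression criteria. The second is that "data completeness in the national audit improves or remains the same". Two purposes are given for it. Together with the first criterion it is a safeguard: "Criteria (1) and (2) are concerned with ensuring the intervention does not have unintended negative consequences". Then a further role is added for this criterion alone: "Criterion (2) is also concerned with feasibility of outcome assessment".

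The first criterion counts people who engage with audit data. The third requires that "50% or more of participants in the questionnaire survey perceive QualDash to be useful" and intend to continue using it. A traffic-light system turns the results into green, amber or red, where amber means feasible with modifications to QualDash.

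Elsewhere, the strengths and limitations list after the abstract says "Issues of data quality may be a limitation of the CITS study", and adds that "data completeness, and whether this changes over the course of the study, will be assessed". The CITS section names the candidate outcomes. For MINAP these are the composite of missed opportunities for care (CMOC), its individual components, angiogram within 72 hours and door-to-balloon time. For PICANet they are non-invasive ventilation first, accidental extubation and unplanned readmission within 48 hours. Of CMOC the section says "This has nine components".

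**The concern.** The rule and its second purpose do not match. A rule that looks only at the direction of change says nothing about the level, and the level decides whether an outcome can be scored in enough patients to carry a trial. Outcome fields that were poorly recorded before QualDash, and stay equally poor after it, satisfy the criterion.

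The criterion is also worded for the audit and does not name the fields that form each candidate outcome. Completeness of the audit can hold steady while one outcome field is poor. Neither of the other two criteria looks at the availability of outcome data.

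At stake is the meaning of a pass. The progression decision leads to the design of a stepped wedge cluster randomised trial, and a pass on criterion 2 could be taken as evidence on outcome assessment that the rule does not provide.

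**Working it through.** The article states no completeness figure, so there is no figure of the plan to reproduce. The check is of the logic of the rule, followed by an illustration with assumed values.

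**1. The rule.** Let *b* be completeness before introduction and *a* completeness after. Criterion 2 passes when *a* − *b* ≥ 0. The level of *a* does not enter.

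**2. The rule against the two purposes.**
- No unintended harm: this asks whether completeness fell, and *a* − *b* answers it.
- Feasibility of outcome assessment: this asks whether *a*, in the fields of the outcome, is high enough. That needs a comparison of *a* with a minimum, and *a* − *b* does not answer it.

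**3. Assumed cases, set against minimum levels of 70%, 80% and 90%** (levels chosen only to show the behaviour of the rule).

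| Before | After | Criterion 2 as written | Minimum of 70%, 80% or 90% |
|---|---|---|---|
| 40% | 40% | pass | fails all three |
| 40% | 41% | pass | fails all three |
| 95% | 94% | fail, read literally | meets all three |

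The rule and a minimum level can disagree in either direction.

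**4. Illustration for a composite.** The number of components, nine, comes from the CITS section. Assume completeness *c* per item, missingness independent between items, all nine items applicable to every patient, and all nine needed to score. The share of records with all nine present is *c*^9:
- 0.98^9 = 0.834, about 83%
- 0.95^9 = 0.630, about 63%
- 0.90^9 = 0.387, about 39%

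Each of these passes criterion 2 if unchanged.

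**5. Sensitivity to the assumptions.** If missing items all fall in the same records, the share is *c* itself: 98%, 95% and 90%. So between independence and full clustering the ranges are 83% to 98%, 63% to 95%, and 39% to 90%. For a component analysed alone, as the CITS section also plans, the share is again *c*.

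**6. Other routes in the protocol.** Completeness and its change are to be assessed, so the level will be known. CITS data are to inform which audits enter the trial, how variable the outcomes are and how long the intervention period should be. None of these passages makes a progression decision depend on the level of completeness.

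**The case against.** The strongest reply is that the protocol says only that criterion 2 is concerned with outcome assessment, not that it is sufficient to establish it. A no-decline rule has some bearing: a shift in completeness at introduction would confound a before-and-after or stepped wedge comparison. Completeness is to be assessed as a level too. Every candidate outcome must be computed monthly over 24 months before and 12 months after introduction, so an outcome that could not be scored would come to light before a trial was designed. How completeness is computed, and the traffic-light cut-offs, are details an article may leave to a fuller document.

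Most of this stands, and it limits the point. A reader might infer that the plan would let an unscorable outcome into the trial. The documents do not support that, because a poor level would be visible and judgement outside the criteria is allowed. A reader might infer that MINAP or PICANet fields are in fact badly incomplete; no figure is given for either. A reader might also fault criterion 2 for not helping to choose between audits, but the protocol gives that task to the CITS data. The absence of cut-offs from the article is not a defect.

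What the reply does not remove is the mismatch. The rule is stated in full, it concerns change, and one of its two stated purposes needs a level. Traffic-light bands placed on a change would not alter that. The authors do set an absolute level in the third criterion, at 50%.

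**Conclusion.** The point holds in a limited form. Criterion 2 does its first job and cannot do its second, and no other progression criterion covers the gap. This rests on the wording of the rule alone and needs no assumption about actual completeness.

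The practical size is unknown. The figures of 83%, 63% and 39% are an illustration under independent missingness with all nine items applicable and required. Clustered missingness, or a scoring rule that tolerates a missing item, would give higher shares. They show that steady, seemingly good item completeness can pass the rule while a composite is fully recorded in far fewer records. They do not show that this happens in either audit.

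The consequence is softened by the commitment to assess completeness, but the formal criterion would still be met at a poor level.

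**What to change.** Keep the no-decline rule as the check on unintended harm. Add a second part to criterion 2: for each candidate outcome (CMOC and its components, angiogram within 72 hours, door-to-balloon time, non-invasive ventilation first, accidental extubation, 48-hour readmission), report the percentage of eligible records in which it can be scored under its own scoring rule. Judge this against a minimum level fixed before extraction, and let the result feed the traffic-light decision.

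The investigators should choose the minimum, since the documents give no basis for a value. It should take account of how each outcome is built: under the assumptions above, a minimum of 75% applied to full recording of the composite would reject it at 95% completeness per item (63%), while a single-field outcome of the same quality would pass. An outcome below its minimum should prompt review of that outcome for the trial, not automatic exclusion.

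The cost is a few lines of text and one extra tabulation from data the CITS already extracts. If extraction is of monthly aggregates, the counts of eligible and scorable records need to be requested with them. The downside is that some outcomes may be rated less favourably than under the present rule.

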## Ethics and dissemination

Written consent will be obtained from participants for interviews and for meeting observations.

Study results will provide initial understanding of how and in what contexts quality dashboards may lead to improvements in care quality. We will disseminate these results to academic audiences, study participants, hospital IT departments and NCAs. If we progress to a trial, in addition to providing further understanding of the impact of quality dashboards on care quality, this will result in wider dissemination of the QualDash software.
